### Measures: Core components

#### Pre-assessment completion of standardised screening questionnaires

For each child, parents/carers will complete one or more of the Ages and Stages Questionnaire 3rd edition (ASQ-3), the Infant Toddler Social Emotional Assessment (ITSEA) and the Childhood Behaviour Checklist (CBCL) (see Table 2 and Additional file 1 for further information). These assess social, emotional and behavioural skills and general development.

**Table 2 Tab2:** Schedule of Standardised developmental assessments by age

	Age of participant		
	24 – 36mo	3y – 6y 11mo	7y +
General Cognition (administered by paediatric psychologist)			
Cognitive Scale from Bayley Scales of Infant and Toddler Development 3rd Ed (Bayley–III)***	✔		
Wechsler Preschool and Primary Scale of Intelligence 4th Ed (WPPSI-IV) Core subtests (30–60 min)		✔	
Wechsler Intelligence Scale for Children 5th Ed (WISC-V) Core subtests (60 mins)			✔
Motor Skills (administered by paediatric occupational therapist or physiotherapist)			
Fine & Gross Motor Scales (Bayley-III)***	✔		
Movement Assessment Battery for Children 2nd Ed (MABC-2)* (20–40 min)		✔	✔
Gross Motor Function Classification Score (GMFCS-E&R) if applicable (5–20 min)	✔	✔	✔
Manual Ability Classification Score (MACS) if applicable	✔	✔	✔
Language and Communication (administered by paediatric speech therapist)			
Receptive & Expressive Scales (Bayley-III)***	✔		
Clinical Evaluation of Language Fundamentals Preschool – 2 (CELF-P2)* Core subtests (30–60 min)		✔	
Clinical Evaluation of Language Fundamentals (CELF-IV) Core subtests (30–60 min)			✔
Communication Function Classification System (CFCS) if applicable	✔	✔	✔
Social/Emotional / Behavioural skills and General Development (parent report questionnaire)			
Infant Toddler Social Emotional Assessment (ITSEA) (25–30 min)	✔		
Child Behavior Checklist (CBCL) (15 mins)		✔	✔
Ages and Stages Questionnaire (ASQ-3)** (10–15 min)	✔	✔	
Academic Achievement (administered by paediatric psychologist)			
Wide Range Achievement Test 4th Ed (WRAT-4) (select subtests) (15–25 min)			✔

*Some younger children may need to be assessed with the previous age group’s instrument; ** Children ≤5 years; ***45–60 min total

#### Medical assessment

Each child will undergo a structured assessment by a developmental paediatrician or paediatric neurologist, including sociodemographics, measurements of height, weight and head circumference, and developmental and neurological status. Clinical history will be obtained from the parent/guardian. Children may be referred for further evaluation (e.g. audiology, blood tests, imaging) if indicated.

Should assessment identify concerns which were previously unknown, parents’ permission will be sought to notify the child’s usual doctor of the findings. Where appropriate, children may be referred for further clinical assessment, opinion or ongoing management.

#### Standardised developmental assessments

Assessments will be tailored to each child’s age, as listed in Table 2. Each instrument is well validated for paediatric use, and normative data are available for comparison with the study group (refer to Additional file 1 for further information). Scores will be calculated using both chronological age, and age corrected for prematurity [30].

### Measures: Optional component

#### Medical information from hospital of birth and subsequent health care providers

Parents will be asked whether they consent to researchers seeking medical information from their child/ren’s hospital of birth, and from subsequent providers of health care.

Seeking background information is important because risk factors which may be associated with neurodevelopmental outcomes may not be known to the parent (such as severity of TTTS, extent of resuscitation required at birth or results of neonatal imaging). Where results of previous developmental assessments (particularly formal IQ tests) are available and are considered reliable and current (undertaken within the past 2 years), such assessments will not be repeated.

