**Methods:**

This paper describes the methodology for a retrospective cohort study in which children aged 24 months and over (corrected for prematurity), who were treated with laser placental photocoagulation for TTTS at Monash Health in Victoria, Australia, will undergo comprehensive neurodevelopmental assessment by a multidisciplinary team. Evaluation will include parental completion of pre-assessment questionnaires of social and behavioural development, a standardised medical assessment by a developmental paediatrician or paediatric neurologist, and age-appropriate cognitive and academic, speech and fine and gross motor assessments by psychologists, speech and occupational therapists or physiotherapists. Assessments will be undertaken at the Murdoch Children’s Research Institute/Royal Children’s Hospital, at Monash Health or at another mutually agreed location. Results will be recorded in a secure online database which will facilitate future related research.

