### Neurodevelopmental outcomes following TTTS

Prevalence of severe neurodevelopmental abnormalities among monochorionic twins who *did not* suffer from TTTS is between 4 and 8% [22]. Survivors of TTTS have been demonstrated to be at further increased risk of adverse neurodevelopmental outcomes. Prior to widespread adoption of SFLP, rates of neurological disability documented among TTTS survivors ranged between 17% [23] and 42% [24].

Van Klink and colleagues [25] summarised 13 studies from 1999 to 2016, reporting neurodevelopmental outcomes following laser surgery. Observed rates of cerebral palsy ranged between 3 and 12%, and rates of neurodevelopmental impairment (cerebral palsy, severe cognitive and/or motor delay (< 2 SD), blindness and/or deafness) were 4–18%. Table 1 summarises an additional 4 studies. Lower prevalence of disability has been identified following briefer periods of follow-up (6 months-2 years) and using less structured review procedures, and higher prevalence with longer duration of follow-up and more rigorous evaluation.

**Table 1 Tab1:** Developmental Outcomes following laser for TTTS (subset of published studies)

Author and year	Number and age of participants	Measures	Outcomes
Campos, D., et al., (2016) [35]	*N* = 33 monochorionic diamniotic twins (post-laser), and *N* = 22 term singletons Birth to 12 months, corrected for prematurity	Bayley Scales of Infant Development, Clinical examination of TTTS group. Two assessments, in first and second 6 months of life.	Cerebral palsy in 18%, strabismus in 9%, microcephaly in 3% of TTTS group. Significant difference between groups in prevalence of cognitive and fine motor deficits apparent by 6 months (greater risk in TTTS group); by 12 months, significantly greater prevalence of deficits in all domains for TTTS group Comparative results at second assessment not provided (table of first assessment repeated in error). Donors 7 times increased risk of adverse outcomes c.f. recipients; donor status and low socioeconomic status, and cardiorespiratory disease were associated with poorer expressive communication & fine motor skills respectively

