Müllers, S. et al., (2015) [36]	*N* = 106 (post-laser). Median age 4 years (range 6 mo – 7 yrs) (correction for prematurity not specified)	Individual correspondence and paediatric evaluation (details not specified)	Ongoing neurodevelopmental concerns in 14% (speech and language concerns *n* = 7, behavioural concerns *n* = 2, mild motor delay n = 2, mild cerebral palsy n = 2, major cerebral palsy n = 2)
Tosello, B. et al., (2014) [29].	*N* = 35 (post-laser). Median age 37 months, mean 30 mo (range 4 mo - 5 yrs)	Neurological assessment at discharge from maternity hospital. Ages and Stages Questionnaire (ASQ) at up to 5 years	As neonates, ≈7% neurologically abnormal (≈93% normal). At follow-up, ≈31% abnormal based on ASQ (≈69% normal), ≈6% severely neurologically abnormal (cerebral palsy). Of children found to be abnormal at follow-up, 45% had not been detected on routine medical review. Donor status and birth < 32 weeks significantly associated with adverse neurosensory outcome as neonates. No correlations at follow-up between outcome and donor status, severity of TTTS or other variables (but small numbers)
Sago, H. et al., (2010) [37]	*N* = 275 (post-laser). Age 6 months (correction for prematurity not specified)	Review of cerebral imaging & clinical assessment by paediatrician (details not specified)	Major neurological disability in ≈5% (severe IVH, cystic PVL, CP, hydrocephalus, ventriculomegaly, or multiple infarcts)

Characterisations of neurodevelopmental outcomes in the literature have been problematic and managed inconsistently, for several reasons. First, developmental status is often reported as a categorical variable (“impaired” vs “unimpaired”), whereas a more conceptually sound framework sees neurodevelopment on a continuum of ability [26]. Further, neurodevelopment is not a single entity, but is conceptualised as comprising a number of domains, any one of which may be impaired either in isolation or in combination. Assigning a child to an “outcome” implies that this outcome is fixed, and ignores that change is fundamental to the construct of neurodevelopment.

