### Participants

The study includes surviving twin (or triplet) child participants, aged 24 months or more (corrected for prematurity), and their parents or carers who will report on the abilities and behaviour of their child/ren. Where survival is not documented or is not known, the family will be approached in a sensitive manner to ascertain eligibility.

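### The two-year rule for reusing earlier developmental tests sets no minimum age at test, so a child under 48 months can carry a domain score from before 24 months

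*Protocol article*

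**What the plan says.** The reuse rule stands under Measures: Optional component, in the section on medical information from the hospital of birth and later providers. It depends on permission: "Parents will be asked whether they consent to researchers seeking medical information from their child/ren’s hospital of birth". The rule then reads "Where results of previous developmental assessments (particularly formal IQ tests) are available" and, where these "are considered reliable and current (undertaken within the past 2 years), such assessments will not be repeated". *Current* therefore means less than 2 years old and nothing more. *Reliable* is not defined. The child's age at the earlier test and the instrument used are not mentioned.

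Three other places bear on it:

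- **Age of the study population.** Participants: "The study includes surviving twin (or triplet) child participants, aged 24 months or more (corrected for prematurity". The abstract likewise describes "a retrospective cohort study in which children aged 24 months and over (corrected for prematurity" who will be assessed.
- **Instruments by age.** The section on standardised developmental assessments ties the tests to the child's age through Table 2, whose youngest band is 24–36 months.
- **Effect of early assessment.** The Background says: "Lower prevalence of disability has been identified following briefer periods of follow-up (6 months-2 years) and using less structured review procedures".

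**The concern.** The look-back is as long as the minimum age. For the youngest children a result can satisfy the rule and still come from infancy, an age that the study otherwise excludes from assessment and for which Table 2 lists no instrument.

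What is at stake is comparability of the outcome. Some children would be scored on a study test at 24 months or later and others on an outside test taken earlier, and the article does not say that the two will be told apart in the analysis. Reuse is also unlikely to be random. The section on the Australian experience says that follow-up was left to treating clinicians and was inconsistent, and release of records needs separate consent. Who has an earlier test may therefore be related to risk. The article wants to inform the choice between follow-up of all survivors and follow-up of a subgroup, and that question is sensitive to such differences in measurement.

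**Working it through.** **1. The plan's own figure.** Number of participants: 100 procedures × 2 fetuses × 0.68 survival = 136 eligible children. This reproduces and is not in dispute.

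**2. Earliest age at a reusable test.** Inputs: look-back of 24 months (reuse rule) and minimum age of 24 months corrected (Participants). For a child seen at age *a* months, the earliest admissible test age is *a* − 24.

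| Age at study (months) | Earliest test age allowed now | Longest look-back if the test must be at 24 months or later |
|---|---|---|
| 24 | 0 | 0 |
| 30 | 6 | 6 |
| 36 | 12 | 12 |
| 42 | 18 | 18 |
| 47 | 23 | 23 |
| 48 | 24 | 24 |

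Since *a* − 24 < 24 whenever *a* < 48, the gap covers every child under 48 months, which is wider than the 24–36 month band.

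**3. How much of the window lies below 24 months.** For *a* between 24 and 48 the share is (48 − *a*)/24. If ages are spread evenly within a band and every date in the window is equally likely (both assumed), the average is the value at mid-band:

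- 24–36 months: (48 − 30)/24 = 18/24 = 75%
- 36–48 months: (48 − 42)/24 = 6/24 = 25%

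These are shares of the window, not shares of children with reused scores.

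**4. Whether the case can arise.** The section on loss to follow-up gives up to 11 years since a 2006 procedure, which implies assessment around 2006 + 11 = 2017. Procedures run to 2015. Time since procedure is then 2017 − 2015 = 2 years for the latest and 2017 − 2013 = 4 years for those of 2013, and the children are somewhat younger than that because birth follows the procedure. So children under 48 months are to be expected. If the 136 were spread evenly over the ten procedure years (assumed), there would be 136/10 = 13.6 per year of age and 2 × 13.6 ≈ 27 aged 24–48 months, before loss to follow-up. That counts children whom the gap could touch. How many have an earlier test is not stated.

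**5. Which outcomes are exposed.**

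- *Three-tier outcome.* Every child still has the study doctor's assessment and the parent questionnaires, and a panel agrees the group. Under Table 3, the unimpaired group requires absence of delay both clinically and on standardised measures, so an old normal score alone cannot place a child there.
- *Domain outcomes.* The article also reports impairment by developmental domain. Where the matching test is not repeated, the reused score is the standardised result for that domain.

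**6. Upper band boundary.** A child seen at 84 months (7 years) may carry a test from 84 − 24 = 60 months (5 years), which lies in the previous Table 2 band. The footnote that permits the previous band's instrument marks MABC-2 and CELF-P2, not the Wechsler tests. This matters less, because such a test was appropriate to the child's age when it was given.

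**The case against.** The strongest reply is that the rule is narrower than it looks. A result must be available with consent and be judged reliable, and formal IQ tests are singled out. In Table 2 the IQ tests begin at 3 years, so the rule seems aimed at older children, and assessors could reject an infancy test. Avoiding repeat testing is itself a sound aim, since it spares families and limits practice effects. All of this stands, and it limits the problem. It does not close it: the wording covers developmental assessments in general, and nothing obliges an assessor to reject a result because of the age at test.

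Four stronger readings are tempting, and the document does not support them.

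- *Any earlier test replaces study testing.* Only the matching test is skipped, and only if judged reliable.
- *The rule contradicts the entry criterion.* The 24-month limit applies to the participant's age, not to the age at a reused test. This is a gap against the purpose of the limit, not a literal contradiction.
- *The bias can be put at a figure.* A reader might take from Table 1 that "Of children found to be abnormal at follow-up, 45% had not been detected on routine medical review", assume 55% detection and half of tests reused, and turn a true 10% into 0.5 × 10% + 0.5 × 5.5% = 7.75%. But the 45% describes routine medical review, not a standardised test. The reuse share is not given, and the sum supposes that the study's own examination, questionnaires and panel recover no missed case.
- *Associations with risk factors are distorted in a known direction.* Children tested early because of worries may be more fully identified, not less. In the same Table 1, one series using Bayley scales and clinical examination in the first 12 months found cerebral palsy in 18%, above the 3–12% in the review cited beside it.

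**Conclusion.** The point holds in a limited form. As written, the reuse rule lets a child under 48 months have a cognitive, motor or language domain score from before 24 months corrected age. This departs from the study's intention to assess from 24 months on. By the article's own account of the literature it would tend to lower the measured prevalence of impairment, although that account combines short follow-up with less structured review, so the effect of age alone is not isolated.

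The effect on the three-tier outcome is limited by the safeguards listed above, and the exposure lies mainly in the domain results. Its size cannot be computed from the document. The figure of about 27 potentially affected children rests on an even spread over procedure years and assessment around 2017. The direction of any distortion of risk-factor associations is not established. The change is worth making because it is cheap, not because a large bias has been shown.

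**What to change.** Reword the rule along these lines: an earlier result is reused only if it was obtained within the past 2 years and at 24 months corrected age or later, with a standardised instrument that Table 2 lists for the child's age at that test, and with standard scores available; otherwise the scheduled test is given.

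In REDCap, record for each domain score its source (study or outside), the instrument and the age at test. Use age at test, not age at the study visit, in the analysis. Repeat the main prevalence and domain results excluding reused scores.

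A stricter rule, demanding the instrument of the child's present band, is harder to defend: it would make more families repeat tests and adds possible practice effects. Recording the instrument and running the sensitivity analysis cover the crossing at 7 years.

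Cost: a few more children are tested by staff already present on the single assessment day, and some families repeat a test. The database already allows earlier reports to be attached, so the added recording is small. The count of 136 eligible children does not change.

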### Outcome measures

#### Outcome by overall neurological status

As has been the case with previous international reports, a three-tiered outcome measure for each child will be allocated (see Table 3). Definitions of these categories will be consistent with previously published reports [31, 32].

**Table 3 Tab3:** Operational definitions of Overall Neurodevelopmental Outcome Groups

Group 1: Unimpaired	Group 2: Mild neurological and/or developmental impairment	Group 3: Severe neurological and/or developmental impairment
NO neurological findings on history / examination, AND no functional impairment	ANY neurological findings on history/examination which are objectively mild or moderate AND which DO NOT result in severe functional impairment *Examples: Strabismus (squint), Mild talipes (club foot), Mild cerebral palsy (GMFCS I-II)*	ANY neurological findings on history/examination which are objectively moderate or severe AND which result in severe functional impairment *Examples: Moderate-Severe cerebral palsy (GMFCS 3–5), Severe visual impairment*
NO neurodevelopmental delay or disability in any domain (either on clinical assessment or according to standardised measures) AND no functional impairment	ANY neurodevelopmental delay or disability (in one or more domain/s, either on clinical assessment or according to standardised measures), which is objectively mild or moderate, AND which DOES NOT result in severe functional impairment *Examples: Mild intellectual disability (IQ 50-70), Mild Autism Spectrum Disorder, Mild Isolated Speech Delay*	ANY neurodevelopmental delay or disability (in one or more domain/s, (either on clinical assessment or according to standardised measures), which is objectively moderate or severe, AND which results in severe functional impairment *Examples: Moderate or Profound intellectual disability (IQ 35–49, or < 30), Moderate or severe Autism Spectrum disorder*

In cases of uncertainty (e.g. moderate gross motor disability (Group 2) but severe functional impairment (Group 3), or severe neurological deficit (Group 3) but moderate functional impairment (Group 2), participants will be classified according to degree of functional impairment.

Medical and allied health clinicians will provide their opinion on each child’s neurodevelopmental status, and assignment of overall neurodevelopmental outcome will be achieved by consensus of a panel of clinicians.

#### Outcome by specific neurodevelopmental diagnosis, developmental domains, and academic achievement

Outcomes will also be categorised by clinical entity (e.g. percentage of children affected by cerebral palsy, including pattern and severity; percentage of children affected by autism, mild or severe). Some children are likely to have more than one diagnosis. Outcomes according to impairment in each of the developmental domains will also be reported, as will results of academic testing for children old enough to participate.

#### Feedback following assessment

Approximately a month following the assessment, parents will receive a brief (2 page) written report by mail, summarising their child/ren’s assessment results. This will be followed by a phone call from a member of the research team within two weeks (parents may opt out of this contact by leaving a phone message or email). In keeping with standard practice among similar research studies, individual children’s numerical assessment scores will not be released unless parents explicitly request this information.

#### Data management

Contact information of potential participants will be recorded on password-protected spreadsheets.

Clinical notes and raw and standardised assessment scores of study participants will be captured by REDCap electronic data capture tools [33] hosted by MCRI. This software allows authorised researchers at distant sites to access the database and add information. With parents’ permission, previous medical reports and images will be able to be attached to child participants’ files. Raw data (including clinical notes, questionnaires and assessment forms) will be retained for the periods prescribed in the MCRI Research Data Storage, Retention & Disposal Policy & Procedure (MCRI4002) (at least until participants reach the age of 25 years).

#### Data analysis

The REDCap database allows information to be transferred to statistical software for analysis. Analysis will be performed on de-identified data. Descriptive statistics will include means and percentages of participants with given outcomes. Data analysis will include Pearson’s χ^2^ and Fisher’s exact tests (when *n* < 5), and 2-factor analysis of variance (ANOVA). Scale variables (such as gestation at birth) will be examined for distribution of scores, with normality testing using Kolmogorov-Smirnov and Shapiro-Wilk tests. Univariate analysis will identify factors associated with outcomes of interest (such as survival without disability), and will include calculations of Odds Ratios. Structured equation modelling will be used to explore the causal pathways and interactions between possible causal factors of adverse neurodevelopmental outcomes. When considering statistical associations and comparisons, the *p* value will be used to assess the strength of association.

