## Abstract

**Background:**

Twin-to-twin transfusion syndrome (TTTS) is a serious complication of 10–15% of twin or triplet pregnancies in which multiple fetuses share a single placenta. Communicating placental vessels allow one fetus (the donor) to pump blood to the other (the recipient). Mortality rates without intervention are high, approaching 100% in some series, with fetal deaths usually due to cardiac failure. Surgical correction using laser photocoagulation of communicating placental vessels was developed in the 1980s and refined in the 1990s. Since it was introduced in Victoria in 2006, laser surgery has been performed in approximately 120 pregnancies.

Survival of one or more fetuses following laser surgery is currently > 90%, however the neurodevelopmental outcomes for survivors remain incompletely understood. Prior to laser therapy, at least one in five survivors of TTTS had serious adverse neurodevelopmental outcomes (usually cerebral palsy). Current estimates of neurological impairment among survivors following laser surgery vary from 4 to 31% and long-term follow-up data are limited.

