### Australian experience with laser surgery, and the Victorian fetal therapy service (VFTS)

The first fetal laser surgery for TTTS in Australia was performed at the Mater Hospital in Brisbane in 2002 [19]. Today, SFLP is offered in four Australian states: Queensland, New South Wales, Western Australia and Victoria. The Victorian Fetal Therapy Service (VFTS) is a three-centre collaboration between Monash Health, Mercy Hospital for Women (MHW) and The Royal Women’s Hospital (RWH), with surgery conducted at Monash Health. Reported outcomes have been consistent with international experience [14, 17, 20, 21], with 68% overall infant survival, and survival of one or more twin/s in 86% of gestations treated.

Regrettably, in Melbourne to date there has been no formal system for routine neurodevelopmental follow-up of surviving children. Although at elevated risk of neurodevelopmental disability, follow-up has been at the discretion of the clinicians involved in the children’s postnatal care. Lack of consistency of follow-up may have resulted in missed opportunities for early detection of developmental difficulties, and valuable information has not been collected.

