#### Number of participants

Approximately 100 procedures have been undertaken within the specified range. Overall survival has been reported at 68% [20]. Assuming twin gestations, approximately 136 children are eligible for the study (100 × 2 × 0.68).

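### The named chi-squared, Fisher and ANOVA tests, and ordinary standard errors for the odds ratios, treat co-twins as independent, so p values for pregnancy-level factors are too small

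*Protocol article*

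**What the plan says.** The Participants section makes the child the unit: "The study includes surviving twin (or triplet) child participants, aged 24 months or more (corrected for prematurity". Co-twins and co-triplets all qualify. The Number of participants section counts the same way: "Approximately 100 procedures have been undertaken within the specified range", and then "Assuming twin gestations, approximately 136 children are eligible for the study (100 × 2 × 0.68".

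The section on the Australian experience reports "68% overall infant survival, and survival of one or more twin/s in 86% of gestations treated".

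On methods, the Data analysis section says: "Data analysis will include Pearson’s χ^2^ and Fisher’s exact tests (when *n* < 5), and 2-factor analysis of variance (ANOVA". It adds factor-by-factor univariate analysis with odds ratios, and structural equation modelling to explore causal pathways. It relies on the p value to judge how strong an association is. It gives no significance level and mentions no confidence intervals.

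The article nowhere refers to pairing, matching, clustering by pregnancy, mixed models, GEE or robust standard errors. Its one remark about comparing children within a set (Potential biases and limitations to feedback) concerns what parents are told.

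**The concern.** Dependence between co-twins is built into this cohort. By the article's own account the children are genetically identical and shared a placenta. They also shared the surgery and usually share a family, and each family is assessed on a single day. The feedback section even uses a pair with IQs of 92 and 89 as an example of children whose true scores are probably about equal.

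An ordinary Pearson, Fisher or ANOVA analysis counts two such children as two independent pieces of evidence. The candidate factors that the article mentions include gestation at birth and severity of TTTS, which are the same for both children of a pregnancy. For these the standard error is too small and false positives rise.

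The article hopes to clarify whether a subgroup of survivors needs routine follow-up. A risk factor that looks convincing only because pairs were counted twice could misdirect that decision.

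**Working it through.** **Inputs from the article.** About 100 procedures, taken as 100 twin pregnancies; 68% overall survival; 86% of pregnancies with at least one survivor; impairment among survivors of 4% to 31% in the literature (abstract).

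**Assumptions, not in the article.** Within-pair correlation ρ of 0.3, 0.5 or 0.7, and a nominal two-sided 5% level.

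**1. The article's own figure.** 100 × 2 × 0.68 = 136 children. This reproduces.

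**2. Pair structure.** Pregnancies with two survivors: 136 − 86 = 50. With one survivor: 86 − 50 = 36. Children with a surviving co-twin: 2 × 50 = 100, and 100/136 = 74%.

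**3. Pregnancy-level factor.** Size-weighted cluster size = (50 × 2² + 36 × 1²)/136 = 236/136 = 1.735. Design effect = 1 + 0.735ρ. Effective number = 136/design effect. Actual error = 2[1 − Φ(1.96/√design effect)].

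**4. Within-pregnancy contrast (for example donor versus recipient, single survivors split 18/18).** Variance factor = 1 − 0.735ρ, put into the same error formula.

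**5. Simulation check** with 50 pairs and 36 single survivors (40,000 runs for Pearson, 20,000 for Fisher). The simulated columns are for a pregnancy-level factor.

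| ρ | Design effect | Effective n | Error, pregnancy-level (formula) | Pearson, 18% outcome | Fisher, 18% outcome | Fisher, 4% outcome | Error, within-pregnancy (formula) |
|---|---|---|---|---|---|---|---|
| 0 | 1.00 | 136 | 5.0% | 5.1% | 3.2% | 0.8% | 5.0% |
| 0.3 | 1.22 | 111 | 7.6% | 7.5% | 5.3% | 1.8% | 2.6% |
| 0.5 | 1.37 | 99 | 9.4% | 9.6% | 6.6% | 2.5% | 1.4% |
| 0.7 | 1.51 | 90 | 11.1% | 11.0% | 7.6% | 3.1% | 0.5% |

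**6. Odds ratio for a pregnancy-level factor.** Two groups of 68 children (25 pairs and 18 single survivors each), outcome 30% versus 15%. True odds ratio = (0.30/0.70)/(0.15/0.85) = 2.43. The median estimate is 2.42 at ρ = 0, 0.5 and 0.9, so clustering does not bias it. Coverage of an ordinary 95% interval is 95.8%, 91.7% and 88.5% respectively.

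**7. Sensitivity.** The abstract gives a higher survival figure: "Survival of one or more fetuses following laser surgery is currently > 90" per cent. Taking 90% with 136 children gives 46 pairs and 44 single survivors. The design effect becomes 1.20 / 1.34 / 1.47 and the error 7.4% / 9.0% / 10.6%. The result hardly moves.

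**The case against.** The strongest reply is that this is a condensed article with an open-ended list of methods, that the analysis plan is not shown, and that the stated aim is descriptive. Percentages and means are not biased by clustering, and no primary hypothesis, significance level or power claim is invalidated. That stands as a limit on severity. It does not remove the point: the article does not merely stay silent but names specific tests, and in their usual form they do not fit the sampling. A later plan that followed the text would carry the fault forward.

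A reader might infer more than the document supports, in five ways:

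- **That every named method is invalid.** Structural equation modelling can accommodate clustering, and so can a two-factor ANOVA with twin set as a factor. The article just does not say that they will.
- **That the odds ratios are wrong.** For a pregnancy-level factor the point estimate is sound; its standard error and p value are not. For donor versus recipient, an unmatched odds ratio is a marginal quantity, different from a matched one rather than mistaken.
- **That planned intervals are too narrow.** No intervals are planned. The warning applies only if they are added.
- **That a planned donor-versus-recipient test will lose power.** Donor status as a risk factor appears only in the summary of earlier studies, so this is conditional on the comparison being made.
- **That error is inflated for every outcome.** Fisher's test starts conservative. At a 4% outcome it stays below 5% even at a correlation of 0.7.

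**Conclusion.** The point holds in a limited form. The named Pearson, Fisher and ordinary ANOVA tests, and ordinary standard errors for the univariate odds ratios, ignore clustering by pregnancy in a cohort where about three quarters of eligible children have a surviving co-twin.

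For pregnancy-level factors, a Pearson-type test meant to have 5% error has roughly 7.6% to 11%, and 136 children carry the information of about 111 to 90. For a within-pregnancy contrast the distortion runs the other way and costs power.

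The pair count follows from the article's figures. The size of the effect depends on the assumed positive correlation of 0.3 to 0.7 and the assumed 5% level. Triplets and loss to follow-up, which the article expects to exceed the 20% of a previous study, would change the pair count.

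Severity is should-fix. Association testing is affected, the descriptive results are not biased, and the remedy can be applied at analysis.

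**What to change.** Amend the Data analysis section so that every association analysis accounts for pregnancy as the cluster. The change must cover the univariate odds ratios and the structural equation models as well as the sentence naming the table tests and ANOVA. Suitable wording would specify:

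- for categorical outcomes, GEE or cluster-robust logistic models with a small-sample correction;
- for scores, linear mixed models with a random intercept per pregnancy;
- for the structural equation models, estimation that allows for clustering by pregnancy;
- for any within-pregnancy contrast, paired or conditional methods;
- cluster-robust intervals, if intervals are reported.

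The cost is wording and standard software; no extra data or participants are needed. Uncertainty for pregnancy-level factors becomes somewhat wider. Very rare outcomes may make the models unstable: at 4%, 136 children give about 5 events (0.04 × 136 = 5.4). The section should therefore say how such outcomes will be handled, for instance by description only.
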